#### *Auditing*

Study data will be analyzed by the PI and study team every three months for 1) continued validity of VSAIL to predict suicide attempt; 2) proper functioning of the VSAIL model [e.g., ensuring all predictors continue to be calculated appropriately for patients]; 3) rates of suicidal ideation and suicide attempt in patients randomized in the study. Because this study necessitates close collaboration with providers receiving BPAs, the study team will have monthly small-group meetings with providers in study sites at VUMC to assess for problems or perceived AEs related to the study protocol, though none are anticipated.

### **9.0 Study Withdrawal/Discontinuation**

Providers may dismiss the BPA and not act on its recommendations at any time. No other intervention is planned. Patients would be unaware of the providers' decisions in that case unless the provider chooses independently to discuss the BPA with them.

### **10.0 Statistical Considerations**

In consultation with the study biostatistician ([name]) and Learning Health System ([name]), the study team determined the following power analysis.

On average at a predicted risk threshold of 2% predicted risk (the highest risk tier in settings without universal screening), 6 patients per day are anticipated in the highest risk tier. Randomizing half to the intervention arm and half to the comparator arm and 15 patients a week per arm, we anticipate 20% of the BPA prompts will be associated with face-to-face affirmation compared to 5% in the comparator arm, which means we need 75 patients in each arm to achieve 90% power with 5% type I error, 200 total, which will require fewer than six months to accumulate. Because prior suicide attempt is rare in this cohort based on diagnostic code ascertainment, simple randomization as above is justified.

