### *Primary Hypothesis*

We hypothesize the Interruptive CDS would be more effective at prompting in-person suicide risk assessment than Non-Interruptive (20% compared to 5%). Thus, we needed at least 75 patients in each arm to achieve 90% power with 5% probability of type I error.

---

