### *Sample Size*

We hypothesize the Interruptive CDS would be more effective at prompting in-person suicide risk assessment than Non-Interruptive (20% compared to 5%). Sample size calculation indicates at least 75 patient encounters are needed in each arm to achieve 90% power with 5% probability of type I error.

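### Under a two-sided 5% test, 75 per arm gives about 80% power rather than the stated 90%, and it does not add up to the 200 total in the same sentence

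*Protocol*

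**What the plan says.** The protocol gives the sample size in three places, each time for 20% against 5%.

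- Primary Hypothesis (under 2.1 Objectives): "we needed at least 75 patients in each arm to achieve 90% power with 5% probability of type I error".
- Sample Size (under 6.0 Study Procedures): "at least 75 patient encounters are needed in each arm to achieve 90% power", again "with 5% probability of type I error".
- 10.0 Statistical Considerations: "we anticipate 20% of the BPA prompts will be associated with face-to-face affirmation compared to 5% in the comparator arm", followed by "we need 75 patients in each arm to achieve 90% power with 5% type I error, 200 total".

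Only section 10.0 gives a total. It also fixes equal allocation and an expected 15 patients a week per arm. No test is named and no sidedness is stated. The hypothesis is worded in one direction: "We hypothesize the Interruptive CDS would be more effective". No dropout or other inflation factor is given, and the Participant Timeline places randomization, intervention and assessment within a single encounter.

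**The concern.** Two things look wrong. First, two equal arms of 75 make 150, yet section 10.0 says 200, and nothing in the protocol accounts for the other 50. Second, 75 per arm is close to the familiar answer for 80% power with these rates, not 90%.

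This is the protocol's only power statement, and it concerns the primary hypothesis. Two of the three places call 75 per arm a minimum and give no total, so a reader of either would take 75 as enough for 90% power. If the trial closed there, its risk of a false-negative result would be about double the risk stated.

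**Working it through.** **Inputs.** p1 = 0.20 and p2 = 0.05 (all three places); type I error 0.05 (all three); power 0.90 (all three); 1:1 allocation (section 10.0). Sidedness is not stated, so two-sided is taken as the convention and one-sided is tried as well.

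**Totals.** 2 × 75 = 150, not 200. 200 / 2 = 100 per arm.

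**Formula.** Two proportions, pooled variance under the null, n per arm:

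n = [z_alpha × √(2 p̄(1 − p̄)) + z_power × √(p1(1 − p1) + p2(1 − p2))]² / (p1 − p2)²

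Here p̄ = 0.125, √(2 × 0.125 × 0.875) = 0.4677, √(0.16 + 0.0475) = 0.4555, and (p1 − p2)² = 0.0225.

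**Trying to reproduce 75 and 200, two-sided 5% (z = 1.960).**

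- 90% power: (1.960 × 0.4677 + 1.2816 × 0.4555)² / 0.0225 = (0.9167 + 0.5838)² / 0.0225 = 100.1 per arm.
- 80% power: (0.9167 + 0.8416 × 0.4555)² / 0.0225 = (0.9167 + 0.3834)² / 0.0225 = 75.1 per arm.

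The figure of 75 comes out at 80% power. The figure of 200 (100 per arm) comes out at 90%.

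**Power at a given n**, by the same formula: Φ[(0.15 × √n − 0.9167) / 0.4555].

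- n = 75: Φ[(1.2990 − 0.9167) / 0.4555] = Φ(0.839) = 79.9%.
- n = 100: Φ[(1.5000 − 0.9167) / 0.4555] = Φ(1.281) = 90.0%.

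**Other two-sided methods.** Required n is rounded up.

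| Method | Power at 75 per arm | Power at 100 per arm | n per arm for 90% |
|---|---|---|---|
| Pooled formula | 79.9% | 90.0% | 101 |
| Unpooled formula | 81.4% | 90.9% | 97 |
| Arcsine | 83.1% | 92.0% | 93 |
| Pooled with continuity correction | not computed | not computed | 114 |
| Chi-square, exact enumeration | 82.7% | 92.1% | not computed |
| Fisher, exact enumeration | 76.0% | 88.3% | not computed |

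No two-sided method comes within 6 points of 90% at 75 per arm.

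**One-sided 5% (z = 1.645).**

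- Pooled formula: (0.7693 + 0.5838)² / 0.0225 = 81.4 per arm for 90%. Power at 75 is 87.8%.
- Unpooled formula: 79 per arm for 90%. Power at 75 is 88.6%.
- Arcsine: h = 2 asin√0.20 − 2 asin√0.05 = 0.4763, so n = 2 × [(1.645 + 1.2816) / 0.4763]² = 75.5. Power at 75 is 89.8%.
- Exact enumeration at 75: chi-square 90.2%, Fisher 85.1%.

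At 100 per arm, one-sided power is 94.6% (pooled) to 95.8% (arcsine and exact chi-square), so a one-sided test does not explain a total of 200.

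**The case against.** The best defence is that sidedness is unstated and the hypothesis is directional. With a one-sided 5% test, the arcsine formula gives 75.5 per arm for 90% power, and the chi-square test has 90.2% power at 75 by exact enumeration. So 75 per arm with 90% power has one coherent reading, and the 80% figure depends on assuming a two-sided test. That dependence is real and must be stated. The reading is weak, though. The protocol never mentions a one-sided test. The pooled and unpooled formulas still need more than 75. By enumeration, the one-sided chi-square test at 75 per arm has a true type I error of 5.9% at a common rate of 5%, so its 90.2% comes at more than the stated 5%. And the total of 200 stays unexplained.

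The second defence is that no trial of 150 is actually planned. The accrual statement in section 10.0 follows directly on the total of 200, and section 12.0 sets six months. At 15 a week per arm, about 26 weeks would bring 26 × 15 = 390 per arm. If either governs, power for 20% against 5% is about 90% or more on these assumptions. This stands to the extent that no loss of power is shown. But the protocol does not say which figure governs, and the other two places give only 75.

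The third point is that the contradiction in totals occurs only in section 10.0. That is correct: Primary Hypothesis and Sample Size carry the power label but not the 200.

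**Conclusion.** The concern holds. The conflict between 75 per arm and 200 in total needs no assumption about the test. Under a two-sided 5% test of 20% against 5%, 75 per arm gives 79.9% power by the pooled formula, and 76.0% to 83.1% across the methods tried. The false-negative risk is therefore about 20% (17% to 24%), against the 10% stated. A single two-sided formula yields both of the protocol's numbers, 75 at 80% power and 100 per arm at 90%. The likeliest explanation is thus that the per-arm figure for 80% was given the label for 90%, although the documents do not prove this. The pairing needs correcting in all three places. If a one-sided test was intended, the text still needs correction, because sidedness is missing and 200 does not follow. These figures treat encounters as independent; clustering by clinician was not part of this check.

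**What to change.** State the test and its sidedness once. Then give the same per-arm number, total and power under Primary Hypothesis, Sample Size and section 10.0. Wording that agrees with the 200 already in the protocol is: 100 per arm, 200 total, 90% power, two-sided 5%, uncorrected two-proportion test, 20% against 5%. If Fisher's test is the planned analysis, 100 per arm gives 88.3%, so the number or the power label must change to match. If 75 per arm is kept as a minimum, write it as 150 total with about 80% power, and say which number ends enrolment.

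The cost is wording only. No patients are needed beyond the stated 200, and 100 per arm at 15 a week takes 100 / 15 = 6.7 weeks, well inside six months. Parts of version 4 are in the past tense. If enrolment has already run, mark the change as a correction of the stated justification and report power for the number actually enrolled as the planning calculation would give it.

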## **11.0 Privacy/Confidentiality Issues**

All study experiments occur solely in the context of already-scheduled clinical care and among patients and providers already intending to interact for purposes of healthcare delivery. No data outside that patient's health record are used in the calculation of VSAIL or in study conduct. Because these interactions occur solely in routine healthcare encounters, the same confidentiality rules apply as in standard of care.

Study data are secured on servers in the VUMC data center or in VUMC Health Information Technology production systems only. These systems are secured via personal, physical, and technical controls including their invisibility to networks outside the VUMC firewall. User credentials are maintained by the VUMC Active Directory and Information Technology and are necessary to access any study data. Only those credentialed and on an approved IRB will have permissions to access study data on these servers. No paper records will be generated nor recorded in this study. All data collection will be digital and will leverage operational clinical systems and EHRs in their generation. No new data collection mechanisms will be required and therefore no new vulnerabilities generated.

## **12.0 Follow-up and Record Retention**

The study will last six months.

As per IRB policy VI.B, all study data will be maintained for six (6) years from the date of the last use of study Protected Health Information (PHI) - at the conclusion of the trial period to identify patients in need of outcome data collection (which is based in EHR queries only).

## **13.0 Ethics and Dissemination**

*Institutional Review Board/Ethics Review Board Approval*

This study was approved by the VUMC IRB #210865.

*Protocol Amendments*

Changes to trial protocols including eligibility criteria, outcomes, or analyses will be communicated to the governing IRB, updated in national registration (ClinicalTrials.gov), clinical trial site leadership and participating clinicians within one calendar day.

*Waiver of Consent – in-clinic preventive CDS*

Waiver of consent was approved by the VUMC IRB (#210865) for the in-clinic CDS components of the trial. This study aims to measure the effectiveness of a risk model-driven BPA on provider behavior. Multiple factors contribute to impracticability to obtain consent. Consenting only those identified at highest risk would itself introduce selection bias and might alter behavior of staff/providers aware that consent had taken place in a manner that would alter study results.

Protocol Version #: 4

Protocol date last updated: 11/9/2023

VUMC IRB #210865

Additionally, the timing of discussing suicidality should be and will be left to providers at the appropriate time in a clinical visit, ideally after some rapport had been established. Informed consent at the start of the visit disrupts that intended workflow. Finally, in the most severe cases of suicidality, decisional capacity might be affected making patient informed consent impossible. Waiver prevents that issue from i) disrupting care for those patients and ii) unduly affecting the study itself.

*Waiver of Consent – minimal risk*

This study does not involve an investigational intervention given or administered directly to patients. This study poses no greater than minimal risk to study participants. VUMC has become a leader in pragmatic, minimal risk clinical trial designs like this one and we have engaged the Learning Health System for high-level guidance in study design. Our study team benefits greatly from the experiences and expertise of our colleagues who have completed similar studies under waiver of informed consent. The potential benefit of this study would come through better provision of screening to those at risk who would not otherwise be screened in current state. Waiver of consent will have no impact on privacy for patients or providers because the CDS will be applied only in routine encounters already scheduled for unrelated reasons, and no data from this study exist outside the bounds of the individuals' EHRs.

*Informed Consent – Post-trial qualitative evaluation*

For those providers who choose to participate, we will email each participant the link to RedCap eConsent form in advance of the interview. The RedCap eConsent framework allows participants the ability to download a copy of their signed consent form. At the start of the interview session, we will review the elements of the informed consent and give participants an opportunity to ask questions of the researcher. During this consent conversation, providers will be reminded that participation is optional and that they may choose to withdraw at any time without any consequences.

*Confidentiality*

Data will be collected from the EHR and stored securely in the VUMC Data Center on servers owned by the study team for later analysis. These systems are designed to securely store Protected Health Information and include encrypted storage, multifactor authentication, and both physical (locked doors, secure facility) and technical (active directory user authentication) controls. Protected Health Information, while necessary to conduct study analyses, will never be exported from these servers or shared.

Data to be collected include the VSAIL-produced probability, the predictors for that probability including historical counts of diagnoses, demographics (age, sex, race, zip code), medication counts, visit utilization (counts of outpatient, inpatient and emergency department visits) for the preceding five years. We will also collect documented and coded suicidality including suicidal ideation (a single

ICD10 code) and suicide attempt (a reference set of ICD10 codes used by our team and others from the CDC Center for National Health Statistics). We will also collect decision support usage statistics included face-to-face screening rates (the Columbia SSRS), and responses to the BPA: 1) "intent to screen" based on the alert; 2) "already screened for suicidality in this visit"; 3) "I disagree with this alert". Additional data will be collected from the same EHR data to evaluate secondary outcome and process metrics following the randomization: emergency department utilization; psychiatric consultation; documentation of suicide screening in clinical notes.

For provider interviews post-trial, we will deidentify all interview data and store data in licensed storage with companies with which VUMC has a Business Associate Agreement (BAA), e.g., Microsoft OneDrive. Data will include impressions of the CDS, its role in decision-making, barriers to its use, and perceived strengths and problems in its design.

#### *Declaration of Interests*

No conflicts of interest exist, financial or otherwise, for any members of the study team relevant to this research.

#### *Access to data*

Only two study team members have access to raw EHR data needed to conduct study analyses: [name] (PI), [name] (developer/analyst). Only members of HealthIT with Physician Builder credentials necessary to design and implement the trial CDS might access EHR data within our vendor EHR: [name] (Physician Builder), [name] (HealthIT).

#### *Ancillary and Post-trial care*

Not applicable to this study.

#### *Dissemination Policy*

Our team will disseminate trial findings through peer-reviewed journals and national conferences in biomedical informatics, psychology, psychiatry, neurology, and potentially emergency medicine and internal medicine. Where possible, the team will preprint our manuscripts at the start of peer review for more transparent dissemination of our results. We will pursue open access publication where available to maximize dissemination.

No professional writers will be employed in dissemination.

Because of the sensitive nature of the PHI needed to conduct this trial, public access to participant-level data will not be possible. Statistical code and the full protocol for the study (this document) will be disseminated with peer-reviewed publication as appropriate.

[name], [name] Lab, <https://www.vumc.org/dbmi>  
Vanderbilt University Medical Center

## **14.0 Appendices**

*Informed consent materials*  
Waiver of consent, as above

*Biological Specimens*  
Not applicable
